# Efficacy and safety of *Onkyeong-tang* in treating cold hypersensitivity in the feet of Korean women: protocol for a double-blind, randomized, placebo-controlled, parallel-group, multicenter clinical study

**DOI:** 10.1186/s13063-020-04265-7

**Published:** 2020-05-18

**Keywords:** Herbal medicine, Cold stress test, Cold hypersensitivity, *Onkyeong-tang*, Randomized clinical trial

## Abstract

**Background:**

Cold hypersensitivity in the hands and feet (CHHF) commonly affects Asian women, especially Korean women, and it negatively impacts the quality of life of the affected individuals. One commonly used herbal prescription for treating CHHF is *Onkyeong-tang* (OKT). Although OKT is widely used clinically in treating CHHF, no randomized clinical trial has been performed to evaluate the efficacy and safety of OKT in the treatment of cold hypersensitivity in the feet (CHF). This clinical trial aims to provide objective evidence for the basis of using OKT in the treatment of CHF in Korean women.

**Methods:**

This trial will be a double-blind, randomized, placebo-controlled, parallel-group, multicenter pilot study. A total of 112 participants will be randomly divided into an OKT treatment group or a placebo group with a 1:1 ratio via a web-based randomization system. The OKT and placebo groups will receive prescribed medications orally three times per day (3 g each time) before or between meals for 8 weeks. The primary outcome studied will be the changes in Visual Analog Scale (VAS) scores of CHF from baseline. Secondary outcomes studied will be the VAS score changes of cold hypersensitivity in the hands, changes in the skin temperature of the hands and feet, total scores of the Korean version of the World Health Organization Quality of Life Scale-abbreviated version, and the results of the cold stress test.

**Discussion:**

This trial will be the first clinical trial to assess the efficacy and safety of OKT in the treatment of CHF. We anticipate that the findings of the study will provide evidence for the basis of using OKT in treating CHF symptoms and generate basic data for designing a further large-scale randomized clinical trial.

**Trial registration:**

Clinical Research Information Service (CRIS): KCT0003723. Retrospectively registered on 8 April 2019.

## Background

Cold hypersensitivity in the hands and feet (CHHF) is defined as “a sensation of coldness in the hands and feet in an environment not considered cold by unaffected people or having a heightened cold sensation in a relatively low temperature area” or “answering ‘cold’ to both are your hands cold or warm? and are your feet cold or warm?” in a previous study [1]. CHHF commonly affects Asian women, especially Koreans, and it negatively impacts quality of life. The prevalence of CHHF has not been investigated in detail, possibly due to the ambiguous diagnostic criteria of the disease. A questionnaire-based analysis revealed that about 38.7% of 318 women in a study experienced cold hypersensitivity [2].

CHHF is typically defined as a subjective symptom, and most patients with CHHF do not present any obvious underlying physiological causes. To treat CHHF, conventional medicines focus on lifestyle management; however, Korean medicine (KM) considers CHHF a key factor for cold pattern identification and offers treatments such as moxibustion and acupuncture, along with various Korean herbal medicines [3–6]. *Onkyeong-tang* (OKT) is one of the commonly used herbal prescriptions for treating CHHF.

The use of OKT dates back to the beginning of the third century, as described in the *Synopsis of Prescriptions of the Golden Chamber*, a classic Chinese medical book written by Zhang Zhongjing. OKT was also introduced with the name *Chokyungsan* in the classic Korean medical book titled *Treasured Mirror of Eastern Medicine* and written by Heo Jun [7]. This herbal formula is used to treat gynecological diseases such as menstrual irregularities, vaginal discharge, uterine bleeding, menopausal disorder, hypoplasia of the uterus, sterility, as well as other conditions such as frostbite and diarrhea [8]. OKT is also used for treating symptoms which result from the deficiency cold of the thoroughfare and conception vessels by warming the meridian to dissipate cold, activate the blood, and also resolve stasis, nourish the blood, and regulate menstruation [9].

Although OKT is widely used in the treatment of CHHF, no randomized clinical trial (RCT) has yet been conducted to evaluate the efficacy and safety of OKT in the treatment of cold hypersensitivity in the feet (CHF). This double-blind, randomized, parallel-group, placebo-controlled, multicenter clinical trial will aim to determine the effects of OKT in patients with CHF. The findings of this study should provide objective evidence from which to evaluate the basis of the clinical use of OKT in the treatment of CHF and provide valuable information to design a large-scale RCT in the future.

## Methods

### Objectives

This study aims to determine the efficacy and safety of OKT in Korean female patients with CHF compared with a placebo group following 8 weeks of administration.

### Study design and setting

This randomized, double-blind, multicenter, parallel-group, placebo-controlled pilot study will be conducted at the Korean Medical Hospital of Sangji University and Semyung University Korean Medical Hospital at Chungju and Jecheon.

A total of 112 participants will be enrolled in this study. The study and control groups will have 56 participants each, and the participants will be registered competitively in the three centers. An adequate explanation and time will be given to all participants so that they can make a thoughtful decision before the principal investigator (PI) or researchers obtain written informed consent. Each participant will undergo a screening period 2 to 7 days prior to randomization. During the screening period, the following will be performed: measurement of vital signs, body index (height, weight, and body mass index [BMI]), body temperature, and CHHF Visual Analog Scale (VAS) score; laboratory tests, chest X-ray, and electrocardiogram (ECG); identifying the reason and method of study participation and collecting demographic, sociological, and gynecological information; evaluation of general physical state; Questionnaire of Pattern Identification; and determining if the potential participant meets the inclusion criteria. Those who meet the inclusion criteria will be invited to take part in the study. Subsequently, participants will be randomly assigned to the OKT or placebo group.

After randomization, all participants will be asked to visit the center every 4 weeks for 12 weeks, and the investigational product (IP) will be administered for 8 weeks. One follow-up visit will be conducted 4 weeks after the completion of medication. A total of five visits will be scheduled over the span of 13 weeks. At visits 3 and 4, the participants will be asked to return any IPs not taken for the purpose of calculating drug compliance. Participants will be asked not to take other medications which could affect the CHF symptoms during the trial (e.g., antithrombotic drugs, psychotropic drugs, antidepressant drugs, drugs for hyperthyroidism, functional health foods such as red ginseng, and blood flow-enhancing over-the-counter drugs). The protocol design is based on the Standard Protocol Items: Recommendations for Interventional Trials (SPIRIT) Checklist (see Additional file 1). Figure 1 shows a schematic flow diagram of the study.

**Fig. 1 Fig1:**
[figure not shown]
Flow chart of the *Onkyeong-tang* (OKT) study

### Randomization

Eligible participants who met the inclusion criteria will be assigned to a treatment group (OKT) or a placebo group with a 1:1 ratio. An independent statistician from the contract research organization (CRO), the Korean Medicine Clinical Trial Center (K-CTC), will perform the randomization. Random assignment numbers will be generated using a web-based randomization system (blockrand package, version 1.3; Intermountain Healthcare, Greg Snow, USA) and will be stratified by hospital. The randomization table of the participants will be retained by the CRO in an opaque sealed envelope throughout the clinical trial period.

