### Procedure

#### Recruitment

A total of 112 subjects who meet the inclusion criteria will be competitively recruited through three Korean medicine university hospitals located in three cities in Korea. The Korean Medical Hospital of Sangji University will recruit 32 subjects, Semyung University Korean Medical Hospital at Chungju will recruit 40 subjects, and Semyung University Korean Medical Hospital at Jecheon will recruit 40 subjects. Each institute will recruit subjects through public outdoor advertisements using posters and other means. Those who are interested in participating in the clinical trial will be invited to contact the CRC or PI to obtain detailed information about the clinical trial and to schedule a screening visit.

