### Outcomes

The primary outcome will be changes in the CHF VAS score from baseline. Secondary outcomes will be the changes in VAS scores for cold hypersensitivity in the hands (CHH), changes in body skin temperature (BT) of the hands and feet, total score of the Korean version of the World Health Organization Quality of Life Scale-abbreviated version (WHOQOL-BREF), and the results of the cold stress test (CST).

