### Sample size calculation

This study was designed based on the assumption that when participants with CHF take OKT, their symptoms would be improved compared to the symptoms of participants who take the placebo. The hypothesis based on this assumption is as follows:
$$ \mathrm{H}0:\updelta =\Delta 1-\Delta 2=0 $$$$ \mathrm{H}1:\updelta =\Delta 1-\Delta 2\ne 0, $$

where:

Δ1 is the average change in VAS score 8 weeks after randomization (within ±3 days) in the OKT group

Δ2 is the average change in VAS score 8 weeks after randomization (within ±3 days) in the placebo group

The sample size calculation was based on the VAS score information of a previously reported clinical trial involving red ginseng [11]. Considering a dropout rate of 20%, we will need to recruit 56 participants in each group to measure the therapeutic effects and to inform the power calculation for a large-scale RCT of OKT in the future.

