### Statistical analysis

The basic statistical analysis method will be the degree of change in the efficacy assessment index between the results of the baseline tests performed before the administration of the test drug and the results of the tests at the end of treatment. The statistical significance level will be set at *P* < 0.05. SPSS for windows version 25.0 (IBM Inc., Chicago, IL, USA) will be used for performing the statistical analysis.

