#### Efficacy

For the efficacy assessment, ITT analysis, a method for including all randomly assigned patients in the analysis regardless of violation or dropout, will mainly be used. Per-protocol (PP) analysis, a method which excludes subjects who do not comply with the study protocol or who have missing data, will also be implemented. The missing values of the efficacy assessment variables will be analyzed using the last-observation-carried-forward (LOCF) method.

A paired *t* test will be used for within-group analysis of the primary and secondary outcome variables. Between-group analysis will be performed using repeated measures ANOVA and the paired *t* test for the primary outcome variable. To measure secondary outcome variables, mean changes in the CHH VAS score, the BT, and the results of the WHOQOL-BREF and CST will be assessed. Repeated measures ANOVA and paired *t* tests will be carried out for the CHH VAS score. A repeated measures ANOVA will also be performed for BT. ANOVA and post hoc analyses will be performed for the WHOQOL-BREF results, and a paired *t* test will be used for the CST results. For the analysis of the Questionnaire of Pattern Identification, ANOVA and post hoc tests will be performed, and for the Questionnaire of Cold Hypersensitivity, Cronbach’s alpha and a correlation analysis will be performed.

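### Randomization is stratified by hospital, but the named efficacy comparisons carry neither hospital nor baseline VAS as a covariate, which costs precision and makes the test conservative

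*Protocol article*

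**What the plan says.** - **Allocation.** The Randomization section assigns patients to OKT or a "placebo group with a 1:1 ratio", and the assignment numbers "will be stratified by hospital". There are three hospitals. Under Recruitment, "The Korean Medical Hospital of Sangji University will recruit 32 subjects" and the two other hospitals 40 each, 112 in total.
- **Outcome.** Under Outcomes, "The primary outcome will be changes in the CHF VAS score from baseline". The hypothesis under Sample size calculation is two-sided and concerns the difference in mean change at 8 weeks; for the active arm, Δ1 "is the average change in VAS score 8 weeks after randomization (within ±3 days) in the OKT group". Table 4 shows the VAS measured at every visit, including visit 2 (day 0).
- **Method.** Under Statistical analysis, "The basic statistical analysis method will be the degree of change in the efficacy assessment index" between baseline and end of treatment. Under Efficacy, "Between-group analysis will be performed using repeated measures ANOVA and the paired" t test for the primary outcome. CHH VAS gets the same pair of methods, BT a repeated measures ANOVA, WHOQOL-BREF an ANOVA with post hoc tests, and CST a paired t test.

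None of these descriptions names hospital as a factor or the baseline value as a covariate.

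**The concern.** Stratifying by hospital balances the arms within each hospital, so differences between hospitals drop out of the treatment contrast. An analysis without hospital leaves those differences in its residual variance. The standard error is then larger than the design warrants, and the test rejects less often than its nominal level.

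Separately, a change score fixes the coefficient on the baseline value at 1. ANCOVA estimates that coefficient, so apart from the degrees of freedom used it is at least as precise. It also accounts for chance baseline imbalance.

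At stake is a wider confidence interval and a less sensitive test for the primary outcome than the collected data would support. The article itself gives reasons to expect hospital differences. Recruitment is competitive across three cities over about two years, and the Discussion says weather may influence the outcomes.

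**Working it through.** **The plan's own figure.** The article states 56 per arm after 20% dropout. It gives no effect size, SD or power, so the core calculation cannot be reproduced. The dropout step gives 56 × 0.8 = 44.8, or about 45 evaluable per arm. Main analysis by ITT with LOCF keeps nominally 56 per arm. Both sizes are used below.

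**Inputs not in the article (assumed).** The baseline to week-8 correlation ρ, the SD ratio k = (baseline SD)/(week-8 SD), the share of outcome variance due to hospital, and a standardized effect of 0.6.

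**Step 1: omitting hospital.** Let s be the hospital share of variance. With balance within hospitals, the true variance of the treatment contrast is (1 − s) times what the unadjusted test estimates. The large-sample rejection rate under the null is therefore 2Φ(−1.96/√(1 − s)).

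- s = 0.10: 1.96/√0.9 = 2.07, rate 0.039
- s = 0.20: 1.96/√0.8 = 2.19, rate 0.028

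Three simulations agree: 0.041, 0.041 and 0.038 at 10%; 0.034, 0.030 and 0.024 at 20%. With no hospital variance the rate was 0.049. With a hospital term it returned to about 0.05. In a simulation of 90 participants and a 0.6 SD effect, adding the hospital term raised power from 82% to 84% (s = 0.10) and from 83% to 88% (s = 0.20). With no hospital variance it made essentially no difference (80.3% and 80.2%).

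**Step 2: baseline covariate, equal SDs (k = 1, week-8 SD = 1).**

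- Change score variance: 2(1 − ρ)
- ANCOVA residual variance: 1 − ρ²
- Ratio: (1 + ρ)/2, a reduction of (1 − ρ)/2

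The reduction is 35% at ρ = 0.3, 25% at 0.5 and 15% at 0.7.

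**Step 3: baseline covariate, unequal SDs.** The general reduction is (k − ρ)²/(k² + 1 − 2ρk). It is zero when k = ρ, because the regression slope is then exactly 1 and the change score is already optimal.

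| k | ρ = 0.3 | ρ = 0.5 | ρ = 0.7 |
|---|---|---|---|
| 1.0 | 35.0% | 25.0% | 15.0% |
| 0.8 | 21.6% | 10.7% | 1.9% |
| 0.7 | 15.0% | 5.1% | 0.0% |

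Inclusion criterion 3 requires a CHF VAS of 4 or more, which can make k less than 1. Simulating that cut-off (latent mean 5 to 7, SD 1.5 to 2, latent correlation 0.4 to 0.7, all assumed) gave k of 0.71 to 0.93 and reductions of about 7 to 25%.

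**Step 4: power.** At ρ = 0.5 and k = 1, the change-score SD equals the outcome SD (√(2 × 0.5) = 1) and the ANCOVA residual SD is √0.75 = 0.866. The standardized effect goes from 0.6 to 0.6/0.866 = 0.693. Two-sided 5% t-based power, deducting three further degrees of freedom for ANCOVA:

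| Per arm | Change score | ANCOVA |
|---|---|---|
| 45 | 80% | 90% |
| 56 | 88% | 95% |

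With a reduction of only 7%, the move at 45 per arm is from 80% to 83%.

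**The case against.** The strongest reply is that the article names families of tests, not model terms. A repeated measures ANOVA can take hospital as a between-subject factor, and a condensed article may leave covariates to the full protocol or the analysis plan. That stands in part: the article does not say that hospital or baseline will be excluded, and a reader who infers a deliberate decision to ignore the strata goes beyond the text. But a t test, named for the primary outcome, CHH VAS and CST, has no place for either term. The basic method is also stated as change from baseline. The point is therefore an improvement to what is written, not a complaint about missing detail.

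Three further objections stand:

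- The change score already uses the baseline value. Only covariate adjustment is absent, so it would be wrong to say that baseline plays no part.
- The 15 to 35% figure requires equal SDs as well as the assumed correlations. It also compares ANCOVA with a two-time-point change score; no gain over the multi-visit repeated measures ANOVA has been computed.
- A power example at 45 per arm alone would overstate what is at stake, since the main ITT analysis nominally has 56.

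Naming a paired t test for two independent arms is a separate problem and is not part of this point.

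**Conclusion.** The point holds as one of efficiency and calibration. A reader might infer that leaving out the stratification factor biases the estimate or inflates false positives. It does not: the unadjusted test is valid and, if hospitals differ, conservative, at about 0.02 to 0.04 under an assumed 10 to 20% hospital share. A reader might also take 15 to 35% as an established loss. The article has no SD, correlation or site variance to support that. The defensible range for baseline adjustment runs from near zero (k close to ρ), through about 7 to 25% under the simulated entry cut-off, to 15 to 35% with equal SDs and ρ between 0.7 and 0.3. The hospital gain is additional and depends on a site variance that is not given. Apart from the few degrees of freedom used, the change score cannot be more precise than ANCOVA, so the direction does not depend on these assumptions. The change is worth making before unblinding, though the trial remains interpretable without it.

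**What to change.** In the Efficacy section, make the primary analysis an ANCOVA of week-8 CHF VAS (or its change from baseline) on treatment, visit 2 CHF VAS and hospital (three levels). Report the adjusted difference with its 95% CI. Use the same form for CHH VAS, BT, WHOQOL-BREF and CST, each with its own visit 2 value.

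The cost is a change of wording and three degrees of freedom: one for baseline and two for hospital. With 90 participants the residual degrees of freedom fall from 88 to 85. If the added terms explained nothing, the penalty on residual variance would be about 88/85 − 1 = 3.5%. No new data, visits or procedures are needed.

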### Blinding

The test medication (OKT) and placebo will be made to appear identical and labeled with the randomization code number. Independent pharmacists or research assistants will administer the trial medications by matching the randomization code numbers to the patients. Clinical trial staff (investigator, research assistants, pharmacist, clinical research coordinator [CRC], clinical research associate [CRA]) and the participants will be blinded to the treatment allocation during the trial. After the end of the trial, the blind will be released for analysis of the results. However, in severe medical emergencies such as serious adverse events (SAEs) during the clinical trial, unblinding may be considered according to the standard operating procedures (SOPs).

### Participants

#### Inclusion criteria

The inclusion criteria are described in Table 1.

**Table 1 Tab1:** Inclusion criteria for the *Onkyeong-tang* (OKT) clinical trial

Inclusion criteria	
1. Female patients between the ages of 19 and 59 years with a complaint of cold hypersensitivity in the feet (CHF)	
2. Patients must meet at least one or more of the following conditions:	
2.1. Symptoms of CHF at a temperature at which most individuals do not feel cold 2.2. Symptoms of severe CHF during exposure to colder than normal temperature 2.3. Persistent CHF symptoms even after returning to a warmer environment	
3. The patient’s Visual Analog Scale score for CHF should be 4 or more	
4. Thermal deviation between the foot (acupuncture point, LR3) and thigh (acupuncture point, ST32) should be higher than 2 °C when both the lower legs are exposed to room temperature (24 °C ± 2)	
5. Patients should be able to give informed consent	

#### Exclusion criteria

The exclusion criteria are listed in Table 2.

**Table 2 Tab2:** Exclusion criteria for the *Onkyeong-tang* (OKT) clinical trial

Exclusion criteria	
1. Those who are taking calcium antagonists or beta-blockers as a treatment for CHHF	
2. Those who are experiencing gangrene or ulceration in one or more fingers	
3. Those who are diagnosed with hyperthyroidism or are currently medicated with thyroid drugs	
4. Those who are diagnosed with autoimmune disease(s)	
5. Those who are diagnosed as having tarsal tunnel syndrome or a positive Tinel’s sign and Phalen’s test	
6. Those who are diagnosed with cervical disc herniation	
7. Those who are diagnosed with diabetes	
8. Those who are taking a drug that may influence CHF (e.g., anticoagulants)	
9. Those with a moderate level of liver dysfunction (aspartate aminotransferase [AST] and alanine aminotransferase [ALT] levels both greater than 100 IU/L) or kidney dysfunction (creatinine [Cr] level greater than 2 mg/dL)	
10. Those unable to give informed consent	
11. Non-pregnant adult women with hemoglobin (Hb) level less than 7 g/dL, hematocrit level less than 26%, and white blood cell (WBC) count greater than 11,000/mm^3^	
12. Those whose average systolic blood pressure (SBP) is 180 mmHg or more or whose diastolic blood pressure (DBP) is 100 mmHg or more when measured twice	
13. Those with suspected arrhythmia, as shown with an electrocardiogram (ECG), or those diagnosed with heart disease, such as ischemic heart disease	
14. Those who are addicted to alcohol or drugs	
15. Those who are pregnant (positive urine human chorionic gonadotropin [hCG]), lactating, or planning for pregnancy	
16. Those diagnosed with malignant tumors	
17. Those taking part in other clinical trials	
18. Those who are unable to understand or speak Korean	
19. Those who are judged to be unfit for the clinical trial by the researchers	

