#### Study schedule

The items to be checked at each patient visit are shown in Table 4.

**Table 4 Tab4:** Study schedule for the *Onkyeong-tang* (OKT) clinical trial

	Screening	Treatment period			Follow-up
	Visit 1 (day − 7 through − 2)	Visit 2 (day 0)	Visit 3 (day 28 ± 3)	Visit 4 (day 56 ± 3)	Visit 5 (day 84 ± 3)
Informed consent	●				
Eligibility criteria	●				
Randomization		●			
Medication compliance			●	●	
Vital signs	●	●	●	●	●
Body measurements^a^	●	●	●	●	●
Collection of demographic, sociological,^b^ and gynecological information	●				
Medical history	●	●	●	●	●
General physical examination	●	●	●	●	●
Thermometer measurement^c^	●	●	●	●	●
VAS	●	●	●	●	●
Monitoring of AE			●	●	●
Questionnaire of Pattern Identification	●				
Questionnaire of Cold Hypersensitivity		●			
Cold stress test		●		●	
WHOQOL-BREF		●		●	
Laboratory tests^d^	●			●	
Chest X-ray & ECG	●				
Medication		●	●		
Test of blindness				●	

^a^ Height, weight, and BMI, but only weight for visits 2, 3, 4, and 5

^b^ Age, occupation, digestion, exercise, smoking, drinking, sleep, etc.

^c^ Thermometer measurement of ST32, LR3, PC8, and LU4 at every visit

^d^ Screening: Hematological examination (WBCs, RBCs, Hb, platelets), blood chemistry test (BUN, Cr, AST, ALT, r-GTP, glucose), thyroid function test (free T4, TSH), urine test, pregnancy test (urine hCG)

Visit 4: Hematological examination (WBCs, RBCs, Hb, platelets), blood chemistry test (BUN, Cr, AST, ALT, r-GTP)

Abbreviations: *AE* adverse event, *ALT* alanine aminotransferase, *AST* aspartate aminotransferase, *BMI* body mass index, *BUN* blood urea nitrogen, *Cr* creatinine, *ECG* electrocardiogram, *r-GTP* gamma-glutamyl transpeptidase, *Hb* hemoglobin, *hCG* human chorionic gonadotropin, *RBC* red blood cell, *TSH* thyroid-stimulating hormone, *VAS* Visual Analog scale, *WBC* white blood cell, *WHOQOL-BREF* World Health Organization Quality of Life Scale-abbreviated version

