### Interventions

After enrollment, the participants will receive 3 g of OKT or placebo three times a day for 8 weeks. Each group will take the designated medicine with warm water before or between meals.

The OKT and placebo will be supplied by Hanpoong Pharm & Foods Co. Ltd, Jeonju, Republic of Korea. We will be using OKT granulated extract which is composed of 1 g of *Evodiae Fructus*, 0.67 g of *Ginseng Radix Alba*, 0.67 g of *Paeoniae Radix*, 0.67 g of *Asini Corii Colla*, 0.67 g of *Cnidii Rhizoma*, 1.67 g of *Pinelliae Tuber*, 0.67 g of *Moutan Cortex Radicis*, 3.33 g of *Liriopis Tuber*, 1 g of *Angellicae Gigantis Radix*, 0.33 g of *Zingiberis Rhizoma*, and 0.67 g of *Glyzzirizae Radix*. These herbal medicines will be extracted and concentrated to 3 g per dose. The placebo granulated extract is composed of 1.7 g of lactose, 1 g of corn starch, 0.1 g of citric acid, 0.1 g of caramel coloring, and 0.1 g of *Ssanghwa* herbal flavor per dose. The placebo will appear identical to OKT in terms of color, shape, weight, flavor, and taste.

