### Safety assessment

To assess safety, vital sign measurement and a general physical examination will be performed at each visit. Renal and liver function tests (blood urea nitrogen [BUN], creatinine [Cr], aspartate aminotransferase [AST], alanine aminotransferase [ALT], and gamma-glutamyl transpeptidase [r-GTP]) and hematological examinations (white blood cells [WBCs], red blood cells [RBCs], hemoglobin [Hb], and platelets) will be conducted at visits 1 and 4. Confirmation of adverse events [AEs] will be performed at visits 3, 4, and 5.

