### Safety

For the clinical laboratory test data, depending on the nature of the variables, ANOVA, *t* test, chi-squared, or Fisher’s exact test will be conducted. The 95% confidence interval for the number of AEs and the percentage of patients who may experience one or more AEs will be calculated within groups and compared between groups. In the case of safety assessment variables, the missing values will be analyzed as missing.

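### The liver exclusion applies only when AST and ALT are both above 100 IU/L, so an isolated rise in one enzyme has no upper limit, although the item is meant to screen out moderate liver dysfunction.

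*Protocol article*

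**What the plan says.** The liver criterion is item 9 of Table 2 (Exclusion criteria). It opens with its purpose, "Those with a moderate level of liver dysfunction (aspartate aminotransferase [AST] and", and completes the definition with "alanine aminotransferase [ALT] levels both greater than 100 IU/L". The same item adds a kidney criterion, joined by *or*. No other item in Tables 1 or 2 sets a limit on AST, ALT or r-GTP. The last item, 19, excludes "Those who are judged to be unfit for the clinical trial by the researchers" and has no threshold.

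The screening panel in Table 4, footnote d, includes "blood chemistry test (BUN, Cr, AST, ALT, r-GTP, glucose), thyroid function test (free T4, TSH"), so both enzymes are known before randomisation. Under Interventions, "the participants will receive 3 g of OKT or placebo three times a day for 8 weeks". Under Safety assessment, renal and liver function tests "will be conducted at visits 1 and 4". Table 3 (Withdrawal criteria) names no liver enzyme. The nearest entries are serious adverse events and the principal investigator's judgement. The Safety analysis section states: "For the clinical laboratory test data, depending on the nature of the variables, ANOVA, *t* test, chi-squared, or Fisher’s exact test will be conducted".

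**The concern.** The criterion and its purpose do not match. An item described as removing moderate liver dysfunction should not admit a woman with a far larger rise in one enzyme than the smallest pair of values that excludes. As worded it does, because *both* requires the two enzymes to exceed the limit together. Item 12 of the same table works differently: a high value on either systolic or diastolic pressure is enough to exclude.

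Two things are at stake. First, a woman with a marked isolated rise meets no numerical exclusion and can enter 8 weeks of treatment. Second, her values then form part of the AST and ALT safety data, where they add spread and are harder to read than those of a woman who started within the limit.

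**Working it through.** **Inputs.** The rule (item 9): AST > 100 and ALT > 100 IU/L. Planned arm size (Study design and setting): 56. The article states no figure for this point, so there is none to reproduce.

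**Step 1: apply the rule to example pairs.** The pairs are illustrative. The last column shows what an either-enzyme connective would do at the same limit.

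| AST | ALT | Item 9 as written | Either enzyme |
|---|---|---|---|
| 40 | 40 | not excluded | not excluded |
| 101 | 101 | excluded | excluded |
| 40 | 101 | not excluded | excluded |
| 101 | 100 | not excluded | excluded |
| 95 | 500 | not excluded | excluded |
| 100 | 1000 | not excluded | excluded |
| 500 | 60 | not excluded | excluded |

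The five rows where the readings differ show the gap. While one enzyme is at or below 100, the other has no ceiling.

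**Step 2: express it as an effective ceiling.** If the AST:ALT ratio is r (below 1), item 9 triggers only when AST = r × ALT exceeds 100, that is, when ALT > 100/r. With r = 0.5 this is 100/0.5 = 200 IU/L. With r = 0.33 it is 100/0.33, about 300 IU/L. These ratios are assumptions; the article gives none.

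**Step 3: possible effect on the spread of the data.** Assume 55 women in an arm with mean ALT 20 and SD 10, plus one woman with value x. Then:

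- mean = (55 × 20 + x)/56
- variance = [54 × 10² + (55/56)(x − 20)²]/55

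| x | Mean | SD |
|---|---|---|
| 101 | 1201/56 = 21.4 | √(11,844/55) = 14.7 |
| 350 | 1450/56 = 25.9 | √(112,355/55) = 45.2 |
| 500 | 1600/56 = 28.6 | √(231,686/55) = 64.9 |

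So one woman could inflate the SD of raw ALT values several-fold. The baseline mean and SD are assumed, and the result applies only if raw values are compared by a mean-based test. If change from screening is analysed, a woman who stays at x contributes a change of 0, and her influence depends only on how far she moves.

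**Step 4: look for another safeguard.** Items 4 (autoimmune disease) and 14 (alcohol or drug addiction) would catch some causes of a raised enzyme but not the finding itself. r-GTP is measured but enters no criterion. Item 19 may be used but need not be. Nothing in Table 3 is tied to a liver enzyme.

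**The case against.** The strongest reply is that item 9 is an explicit definition, no other section contradicts it, and the sponsor may have wanted a joint condition. The enzymes are seen before randomisation, history and physical examination are also taken, and a researcher would have to look at a large isolated rise and accept it. After entry, examination continues: "To assess safety, vital sign measurement and a general physical examination will be performed at each visit". This stands in part. It means that such a woman *can* be randomised, not that she *will* be. It does not close the gap, because item 19 is discretionary and carries no threshold.

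A reader might infer more than the documents support:

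- *That her visit 4 value is uninterpretable.* She has a visit 1 value, and there is a blinded, randomised placebo arm, so change can be examined.
- *That the liver comparison is biased.* Randomisation balances such women on average. What remains is noise and possible chance imbalance.
- *That one or two such women would hide a real difference.* The Safety section lets the test depend on the variable and does not fix a comparison of raw means. Step 3 is an illustration, not a prediction.
- *That the absence of laboratory tests between visits 1 and 4 belongs to this defect.* That schedule applies to every participant and is a separate choice, which changing item 9 would not affect.

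Timing also counts. The article appeared on 18 May 2020 and Trial status expects recruitment to finish that month, so a change to screening may reach almost nobody. This is why the fix has a second part.

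**Conclusion.** The point holds in a limited form. As written, item 9 leaves an isolated AST or ALT rise uncapped, which does not serve its stated purpose, and the only backstop is discretionary. This follows from the wording alone and rests on no assumption.

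The size cannot be estimated. The article gives no frequency of isolated rises, the number of women is probably small, and the ratios and ALT distribution used above are assumed. The consequence is for participant safety and the precision of the liver safety data. The primary outcome, the VAS score for cold feet, is not affected. The correction is worth making because it is cheap and concerns participant safety, not because the trial's conclusions depend on it.

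**What to change.** 1. **Table 2, item 9.** The sponsor should reconcile the connective *both* with the item's stated purpose, so that an isolated rise above the sponsor's own limit is not left uncapped. The 100 IU/L limit stays as the sponsor set it; no other limit is proposed here. If the joint condition was deliberate, the protocol should say so and say how an isolated rise is handled.
2. **Women already enrolled.** Use the existing visit 1 results to identify those with one enzyme above 100 IU/L and the other at or below it. Report their number by arm and site, and their visit 1 and visit 4 liver values separately.
3. **Safety analysis.** State that AST and ALT are analysed as change from the screening value, or adjusted for it, so that a high starting value is not read as an effect of treatment.

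The cost is a short amendment if screening is still open, a few more screen failures, and a little analysis work. No new test is needed, because AST and ALT are already measured at visits 1 and 4.
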